### Sample size

Sample size calculation was performed using the Coma Recovery Scale-Revised (CRS-R) score as the primary outcome measure. We employed a one-way analysis of variance (ANOVA) model to determine the required sample size (25). Calculations were conducted using G*Power software (version 3.1.9.7, University of Düsseldorf, Germany) (26).

Based on previous similar studies (14, 27), we assumed a clinically significant difference of 4 points in CRS-R scores between the treatment and control groups. This threshold is based on previous research by Estraneo et al. (24), which demonstrated that a 4-point change in CRS-R score is associated with meaningful transitions between diagnostic categories and correlates with clinically observable improvements in patient responsiveness and function, with a standard deviation of 7.3 points. The significance level (*α*) was set at 0.05, and the power (1-*β*) at 0.8, which are commonly used parameters in clinical trials (28).

For a 3 × 6 mixed repeated measures ANOVA (one 3-level between-subjects factor and one 6-level within-subject factor), G*Power calculated a required sample size of 22 participants per group to detect a medium effect size (*f* = 0.25) with 80% power at a 5% significance level, considering correlations among repeated measures of 0.5 and a nonsphericity correction of 0.75. To account for potential dropouts and loss to follow-up, we increased the sample size by 20% (19, 29). Consequently, the final sample size was determined to be 27 participants per group, totaling 81 participants for the three-group study design.

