### Outcome measures

#### Primary outcome measure

The primary outcome measure is the change in total score on the Coma Recovery Scale-Revised (CRS-R) from baseline to post-treatment (24). The CRS-R is the gold standard for assessing patients with disorders of consciousness and comprises six subscales: auditory, visual, motor, oromotor, communication, and arousal, with a total score range of 0–23 (32). CRS-R assessments will be conducted by trained evaluators at baseline, after 4 weeks of treatment, and at 2 weeks, 4 weeks, 12 weeks, and 24 weeks post-intervention. To ensure consistency and accuracy, all evaluators will undergo standardized training and pass a video scoring test to ensure inter-rater reliability (ICC > 0.8) (24).

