### Statistical analysis

#### Analysis principles

This study will employ intention-to-treat (ITT) analysis as the primary analytical approach to evaluate the efficacy of transcranial direct current stimulation combined with median nerve stimulation in patients with chronic disorders of consciousness (38). The ITT analysis will include all randomized patients, regardless of protocol adherence or treatment completion. Additionally, we will conduct a per-protocol (PP) analysis as a supplementary measure to assess treatment effects in patients who fully adhered to the study protocol (39).

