#### Statistical methods

(1) Descriptive statistics: Continuous variables will be presented as mean ± standard deviation (for normally distributed data) or median and interquartile range (for non-normally distributed data); categorical variables will be presented as frequencies and percentages.

(2) Between-group comparisons: Baseline characteristics: Continuous variables will be compared using one-way analysis of variance (ANOVA) (for normally distributed data) or Kruskal-Wallis test (for non-normally distributed data); categorical variables will be compared using chi-square test or Fisher’s exact test.

(3) Primary outcome analysis: First, within-group comparisons will be conducted to assess changes in CRS-R scores from baseline to each follow-up time point within each intervention group. Paired t-tests (for normally distributed data) or Wilcoxon signed-rank tests (for non-normally distributed data) will be used for these comparisons. This will provide insights into the therapeutic effectiveness of each intervention approach. Subsequently, between-group comparisons will be performed using a 3 × 6 mixed repeated measures analysis of covariance (ANCOVA) with group (tDCS+MNS, sham tDCS+MNS, and tDCS+sham MNS) as a between-subjects factor and time (baseline, 4 weeks post-treatment, and follow-ups at 2 weeks, 4 weeks, 12 weeks, and 24 weeks) as a within-subjects factor. To control for potential confounding variables, baseline age, sex, duration of consciousness disorder, and baseline severity will be included as covariates if significant differences are observed at baseline despite randomization. Post-hoc analyses with appropriate multiple comparison corrections will be used to identify specific group differences at each time point. The analysis will include all assessment time points (baseline, 4 weeks post-treatment, and follow-ups at 2 weeks, 4 weeks, 12 weeks, and 24 weeks) (40). If data violate normality assumptions, generalized estimating equations (GEE) models will be employed (41).

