(4) Secondary outcome analyses: For continuous secondary outcomes (e.g., fNIRS, EEG, and ERP metrics), both within-group and between-group analyses will be conducted following the same approach as the primary outcome. Within-group changes will be assessed first, followed by between-group comparisons with appropriate covariate adjustments. Categorical secondary outcomes (e.g., GOS-E) will be analyzed using ordinal logistic regression, with baseline measurements included as covariates to account for potential confounding.

(5) Missing data handling: Multiple imputation techniques will be used to handle missing data, reducing bias and improving statistical power, The imputation model will include all primary and secondary outcomes, as well as key baseline covariates (age, sex, time since injury, baseline CRS-R score, and consciousness state). We will generate 20 imputed datasets, as recommended by methodological guidelines (42); Results will be pooled using Rubin’s rules, and sensitivity analyses will include complete case analysis to assess the impact of missing data on results.

(6) Subgroup analyses: Pre-specified subgroup analyses will be conducted based on age, sex, duration of consciousness disorder, and baseline CRS-R scores to explore potential effect modifiers. To control for multiple comparisons in these subgroup analyses, we will apply the same Bonferroni correction approach used for secondary outcomes. Furthermore, we will clearly label these analyses as exploratory and interpret the results with appropriate caution regarding potential Type I error inflation.

(7) Sensitivity analyses: In addition to ITT analysis, PP analysis will be performed to evaluate treatment effects in patients who fully adhered to the protocol.

(8) Covariate handling: Despite our stratified randomization strategy, potential imbalances in baseline characteristics might still exist. Therefore, we will compare baseline demographic and clinical characteristics between groups. If any significant differences are detected (*p* < 0.05), these variables will be treated as covariates in subsequent analyses to minimize confounding. Additionally, baseline measurements of outcome variables will routinely be included as covariates in the respective analyses to account for potential regression to the mean effects and to increase statistical power.

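### The imputation model, as listed, leaves out treatment arm; if the treatment works, imputed CRS-R values will understate the between-arm difference

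*Protocol article*

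**What the plan says.** Under Statistical methods, item (5), the protocol article sets out the imputation: "The imputation model will include all primary and secondary outcomes, as well as key baseline covariates (age, sex, time since injury, baseline CRS-R score", plus consciousness state. It continues: "We will generate 20 imputed datasets", pooled by Rubin's rules, and "sensitivity analyses will include complete case analysis to assess the impact of missing data on results". Neither this item nor any other section mentions treatment arm in the imputation or says that imputation is done within arm.

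The imputed data feed a comparison of arms. Item (3) of the same section states: "between-group comparisons will be performed using a 3 × 6 mixed repeated measures analysis of covariance (ANCOVA) with group" as the between-subjects factor. Analysis principles makes intention-to-treat the primary approach: "The ITT analysis will include all randomized patients, regardless of protocol adherence or treatment completion". The outcome is defined under Primary outcome measure: "The primary outcome measure is the change in total score on the Coma Recovery Scale-Revised (CRS-R) from baseline to post-treatment". The visit schedule places post-treatment at Week 4.

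**The concern.** An imputation model should contain every variable whose effect the analysis will estimate. If arm is left out, a missing CRS-R value is predicted as though arm made no difference beyond what the other variables in the model already show. Under randomisation the five baseline covariates carry no systematic information about arm. For a patient with no post-baseline data, the imputed value therefore has the same expected value, given baseline, whichever arm the patient was in. Completed data that mix real values with such imputed values understate a true difference.

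This bears on the primary estimate, because the primary set is all randomised patients and the imputed values go straight into the group comparison. Item (5) gives the purpose of imputation as less bias and more power; the model as listed works against both when the treatments differ.

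**Working it through.** **The plan's own figures.** The article states no number for the effect of imputation, only the sample size and its dropout allowance. For the group-by-time interaction (f = 0.25, 3 groups, 6 visits, nonsphericity 0.75) with 22 per group, the noncentrality is 0.25² × 66 × 5 × 0.75 = 15.47. Under one of G*Power's effect-size options this gives power 0.810, so 22 is reproduced. The allowance is 22 × 1.2 = 26.4, rounded up to 27.

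**Inputs from the Sample size section.** Difference Δ = 4 points, SD 7.3, correlation between visits 0.5, 27 per arm. The 20% missing used below is borrowed from the dropout allowance ("we increased the sample size by 20" per cent); it is not a forecast of loss before Week 4.

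**Assumptions not in the documents.** Data missing completely at random, equal correlation between all visits, the same effect at every post-baseline visit, the two control arms equal, and secondary outcomes left out of the simulated model.

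**Which patients have nothing that reveals arm.** In Table 1, fNIRS, EEG and ERPs have their only post-baseline measurement at Week 4, GOS-E is first repeated at Week 8, and fMRI is repeated only at Week 28. A patient lost before Week 4 therefore has no post-baseline value of any outcome.

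**Expected attenuation at Week 4.** If a fraction m has no post-baseline data, the expected difference without arm is (1 − m) × Δ + m × 0.

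- All loss before Week 4: m = 10%, 20%, 30% gives 3.6, 3.2, 2.8.
- 20% dropout spread evenly over the five post-baseline visits: m = 20%/5 = 4%, so the loss is 0.04 × 4 = 0.16 and the expected difference 3.84.

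**Simulation.** Twenty Bayesian-regression imputations, ANCOVA on baseline at the visit concerned (a simplification of the 3 × 6 model), Rubin pooling, 400 replicates. The Monte Carlo standard error of a mean estimate is about 0.09: 7.3 × √(1 − 0.5²) × √(2/27) = 1.72, and 1.72/√400 = 0.086.

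| Scenario (true difference 4.0) | Without arm | With arm | Loss |
|---|---|---|---|
| 10% lost, all before Week 4 | 3.60 | 4.02 | 0.42 |
| 20% lost, all before Week 4 | 3.17 | 3.98 | 0.81 |
| 30% lost, all before Week 4 | 2.66 | 3.88 | 1.22 |
| 20% dropout spread over visits, Week 4 | 3.78 | 3.94 | 0.16 |
| 20% dropout spread over visits, Week 28 | 3.62 | 4.05 | 0.43 |
| 20% miss only the Week 4 visit | 3.74 | 3.96 | 0.22 |

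Both methods were run on the same simulated trials, so the loss column is more precise than either mean alone. It agrees with the formula: 0.4, 0.8 and 1.2 for early loss, 0.16 for spread loss. A further simulation gave about 3.5 at Week 28 with spread dropout, hence the range of 0.4 to 0.5 there.

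**Power and type I error at Week 4, one pairwise comparison, 20% missing.** Early loss: power 0.31 without arm, 0.52 with arm. Spread loss: 0.55 and 0.60. With no true difference and early loss, the mean estimate without arm is −0.03; the rejection rate is 0.022 without arm and 0.055 with it.

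**The case against.** **The list may not be exhaustive.** It says what the model includes, not that nothing else enters. Arm is neither an outcome nor a baseline covariate, and a fuller analysis plan may add it. This is fair, and it is why the point is conditional on the text being followed as written. It does not remove the point. The article goes as far as naming five covariates, the number of imputations and the pooling rule, and a programmer working from it would leave arm out.

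**A reader might infer that all missing values come from one distribution common to the three arms, so that the difference always shrinks in proportion to the missing fraction.** The documents do not support that. The listed model contains all outcomes, so CRS-R scores observed at other visits carry part of the arm information. Proportional shrinkage holds only for patients with no post-baseline data. The allowance in Sample size covers dropout and loss over the whole trial; the retention measures and the home or video visits also make it unlikely that all of it falls before Week 4. The 0.8-point figure is therefore an upper end at 20% missing, and no 30% scenario appears in the documents.

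**A reader might also infer that the model is too large for 81 patients.** One metric per modality gives 6 + 2 + 2 + 2 + 3 + 2 = 17 outcome variables. Chained regressions with these 17 and 4 covariates in 81 patients, at 20% dropout and with assumed correlations, ran without a fitting failure in 120 replicates. The article does not fix how many metrics each modality supplies. Instability is not shown and is not part of this point.

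**The complete-case analysis is a safeguard.** In part: if data are missing completely at random it is unbiased and would expose the attenuation. It is only a sensitivity analysis and leaves the primary estimate as it is.

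**Conclusion.** The point holds as a badly fixed specification: the variables are enumerated and the one the analysis compares is missing. The direction is not in doubt if the list is followed and the treatments differ. At 20% missing, the Week 4 difference of 4 points loses between about 0.2 points (0.2/4 = 5%) and about 0.8 points (0.8/4 = 20%), depending on how early patients are lost.

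It would be wrong to conclude that the trial risks a false positive from this source. With no true effect the estimate is unbiased and the test rejects too seldom. The harm is an understated effect and lost power when the combination works.

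The sizes rest on the assumptions listed with the calculation. Secondary outcomes in the model could carry further arm information and reduce the loss somewhat; a different pattern or amount of missing data would change it.

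**What to change.** Add one sentence to Statistical methods, item (5): the imputation model includes treatment arm, with effects that may differ by visit; or imputation is done separately by arm. In chained equations the first means entering arm as a factor in the equation for each visit. It is the more practicable choice, since imputing by arm leaves at most 27 patients for each fit.

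Blinding is unaffected: the Study design section already codes the groups A, B and C until analysis is complete, and imputation needs only that code. The change needs no new data or visits and should be made before any imputation is run. If a separate analysis plan already includes arm, the article's list should be brought into line with it. Fewer auxiliary outcomes, or a separate imputation model per modality, is an optional preference.

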#### Secondary outcome measures

(1) Functional Near-Infrared Spectroscopy (fNIRS): To assess cortical hemodynamic changes, reflecting brain functional connectivity (33). Measurements will be taken at baseline and after 4 weeks of treatment.

(2) Electroencephalography (EEG): To evaluate changes in brain electrical activity, including power spectral analysis and functional connectivity analysis (34). Measurements will be taken at baseline and after 4 weeks of treatment.

(3) Event-Related Potentials (ERPs): To assess cognitive processing abilities, focusing on the P300 component (35). Measurements will be taken at baseline and after 4 weeks of treatment.

(4) Glasgow Outcome Scale-Extended (GOS-E): To evaluate overall functional outcomes (36). Assessments will be conducted at baseline, 4 weeks, and 12 weeks follow-up.

(5) Functional Magnetic Resonance Imaging (fMRI): To be assessed at baseline and 24 weeks follow-up.

(6) Adverse Events: All treatment-related adverse events will be recorded, including type, severity, and duration. Continuous monitoring will be conducted during each treatment session and throughout the follow-up period.

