All statistical analyses will be conducted using R software (version 4.1.0 or higher), with a significance level set at *α* = 0.05 (two-sided). To control for Type I error inflation due to multiple comparisons, Bonferroni correction will be applied to adjust *p*-values for secondary outcomes (43).

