The combined application of tDCS and MNS may promote consciousness recovery in pDoC patients through multiple mechanisms. Based on our stimulation sites (left dorsolateral prefrontal cortex at F3 position and right supraorbital area at Fp2 position), we have specific predictions regarding the neural effects and potential recovery mechanisms. tDCS may modulate cortical excitability by altering the resting membrane potential of neurons (13), potentially enhancing neuroplasticity and influencing neuronal activity through regulation of neurotransmitter release. We predict that anodal stimulation at the left DLPFC will enhance the excitability of this region, which plays a crucial role in executive functions and consciousness processing (50).

These mechanisms may contribute to the reconstruction of damaged neural networks and restoration of functional connectivity within specific brain circuits critical for consciousness (13, 51, 52). Specifically, we predict enhanced connectivity between: (1) left dorsolateral prefrontal cortex and bilateral thalamus, (2) left dorsolateral prefrontal cortex and posterior parietal cortex, and (3) medial prefrontal cortex and posterior cingulate cortex. These connectivity changes would reflect improved integration within the frontoparietal network and default mode network, both of which are often disrupted in pDoC patients (53, 54).

MNS, by stimulating the peripheral nervous system, can activate the ascending reticular activating system (ARAS) that maintains wakefulness and consciousness, while also promoting the release of neurotrophic factors (such as brain-derived neurotrophic factor, BDNF) that support neuronal survival and growth (55, 56). Through median nerve stimulation, we expect to observe increased activity in the somatosensory cortex, which may facilitate improved sensory processing and integration–key components for consciousness recovery (57).

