The combined application of these two techniques may produce synergistic effects: tDCS-induced changes in cortical excitability may enhance the conduction and integration of MNS signals in the central nervous system, while MNS may enhance the effects of tDCS by increasing cortical responsiveness (48, 58). This synergy may more effectively promote the reorganization of brain functional networks (such as the default mode network and salience network) involved in maintaining consciousness (59). Furthermore, this combined therapy may act by modulating neuroinflammation and oxidative stress. Studies have shown that tDCS can reduce the expression of inflammatory factors, while MNS can regulate the autonomic nervous system, thereby influencing systemic inflammatory responses (60, 61). This anti-inflammatory action may help create a more favorable environment for neural repair. In summary, the combined application of tDCS and MNS may promote consciousness recovery in pDoC patients through multiple mechanisms, including modulating neuroplasticity, activating ARAS, promoting neurotrophic factors, reorganizing functional networks, and regulating neuroinflammation. This multi-target therapeutic strategy may be more effective than single interventions in addressing the complex pathophysiological characteristics of pDoC.

Our secondary outcome measures directly evaluate hypothesized mechanisms of tDCS+MNS effects. EEG analyses will assess cortical excitability and network reorganization in consciousness-critical frontoparietal and default mode networks. Event-related potentials (P300) will measure cognitive processing improvements. fNIRS will provide insights into vascular and metabolic changes, while fMRI will evaluate network connectivity changes, particularly in thalamocortical circuits and the ascending reticular activating system. By systematically analyzing these multiple physiological parameters, we can triangulate evidence to support or refute our mechanistic hypotheses regarding neuroplasticity, thalamocortical connectivity restoration, and anti-inflammatory effects.

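### Single-step Bonferroni for the secondary outcomes is valid, but Holm's procedure gives the same 5% family-wise control and never rejects less, so a small trial gives up some power

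*Protocol article*

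**What the plan says.** The last paragraph of Statistical methods sets a two-sided 0.05 level and states that "Bonferroni correction will be applied to adjust *p*-values for secondary outcomes". It does not give the number of tests in the family. Item (6) of the same section extends the rule to subgroups: "we will apply the same Bonferroni correction approach used for secondary outcomes". It also labels the subgroup analyses exploratory. Item (4) covers the secondary outcomes themselves: "For continuous secondary outcomes (e.g., fNIRS, EEG, and ERP metrics), both within-group and between-group analyses will be conducted", following the approach laid down for the primary outcome. That approach comprises paired tests within each arm, a three-group comparison, and post-hoc group contrasts with a multiplicity correction.

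The section on secondary outcome measures lists fNIRS, EEG, ERPs (the P300), GOS-E and fMRI, with adverse events as a sixth entry. The Discussion says of these measures that "we can triangulate evidence to support or refute our mechanistic hypotheses".

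**The concern.** Single-step Bonferroni holds every test to the strictest threshold, even after other hypotheses in the family have been rejected. Holm relaxes the threshold after each rejection and keeps the same guarantee. Choosing the single-step version therefore costs power and gains nothing in error control.

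This matters here because the trial is small. The Sample size section plans 22 evaluable patients per group and 27 randomised, with power set for the CRS-R and not for the secondary measures. If several of the neurophysiological and functional measures do respond to the combined treatment, which is what the Discussion expects, the plan will miss some of those effects that an equally strict procedure would find.

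**Working it through.** **Inputs from the article.** Two-sided alpha 0.05 (Statistical methods). 22 per group before dropout (Sample size). A 20% increase gives 22 × 1.2 = 26.4, rounded up to 27, and 3 × 27 = 81; this agrees with the stated figures. The multiplicity sentence has no figure of its own to reproduce beyond 0.05.

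**Assumptions.** Five tests, one for each secondary efficacy outcome, leaving out adverse events. A standardised difference of 0.8 for each real effect, because the article gives none for these outcomes. Each test is taken as a two-arm t-test, a simplification of the three-group comparison. Correlation between endpoints is 0 or 0.5.

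**Step 1: thresholds.** Bonferroni compares every p-value with 0.05/5 = 0.01. Holm orders the p-values and compares them in turn with 0.05/5 = 0.01, 0.05/4 = 0.0125, 0.05/3 = 0.0167, 0.05/2 = 0.025 and 0.05, stopping at the first failure.

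**Step 2: Holm never rejects less.** If a p-value is at most 0.01, so are all smaller ones. Each passes its Holm threshold, none of which is below 0.01. So every Bonferroni rejection is a Holm rejection. The first thresholds are equal, so the chance of at least one rejection is identical.

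**Step 3: same error guarantee.** Suppose m₀ of the five null hypotheses are true. When Holm first rejects a true one, at least m₀ hypotheses are still in play, so the threshold is at most 0.05/m₀. The chance that any of the m₀ true nulls falls below that is at most m₀ × 0.05/m₀ = 0.05, whatever the correlation.

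**Step 4: size of the gain.** Simulated average power over the real effects (at least 40,000 replicates per scenario; ranges span correlation 0.5 and 0):

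| Real effects of 5 (difference 0.8) | Per arm | Holm | Bonferroni |
|---|---|---|---|
| 5 | 27 | 0.71–0.73 | 0.61 |
| 3 | 27 | 0.64–0.65 | 0.60–0.61 |
| 1 | 27 | 0.61 | 0.60–0.61 |
| 5 | 22 | 0.59 | 0.49 |
| 3 | 22 | 0.53 | 0.49 |
| 1 | 22 | 0.49 | 0.49 |

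As a lower effect size, take the CRS-R assumption in the Sample size section: 4/7.3 = 0.548. With all five effects real and independent, Holm versus Bonferroni is 0.31 versus 0.27 at 27 per arm and 0.23 versus 0.20 at 22.

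**Step 5: error rates in the simulation.** With all five nulls true, both methods give about 0.049. With three real effects, 27 per arm and independent tests, the chance of rejecting at least one of the two true nulls is 0.036 under Holm and 0.020 under Bonferroni. Holm uses more of the permitted 5% but stays within it.

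**Step 6: does the family count matter?** Only conditionally. Suppose the divisor were five while more endpoints were tested. Counting EEG as 2, fNIRS 1, P300 1, GOS-E visits 2 and connections 3 gives 9; counting fNIRS twice gives 10. For one three-group test each at 0.01, independence gives 1 − 0.99⁹ = 0.086 and 1 − 0.99¹⁰ = 0.096. At correlation 0.5 it is about 0.07–0.075, and at 0.8 about 0.043–0.048. The range is thus roughly 0.04 to 0.10. If instead the divisor equals the number of tests, say nine, independence gives 1 − (1 − 0.05/9)⁹ = 0.049.

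**The case against.** The strongest defence is that Bonferroni is a recognised and conservative choice, so nothing in the plan is wrong. That stands. It is also fair that the gain depends on effects the article does not quantify: it vanishes if only one effect is real and is a few points if the effects are modest. Holm also lacks the simple simultaneous confidence intervals that come with Bonferroni. These points limit the importance of the change. They do not make the single-step rule preferable for testing.

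A reader might go further and infer that the plan divides by the number of outcomes, tests several endpoints within each, and so fails to hold 5%. The documents do not support this:

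- No divisor is stated. Adjusting every secondary p-value fits the sentence equally well and keeps the error at or below 5%.
- Nothing suggests that the divisor would be chosen after the data are seen.
- The outcomes are not uniformly bundles of tests. ERPs are narrowed to the P300, and only GOS-E has more than one post-baseline visit. EEG is described as "including power spectral analysis and functional connectivity analysis", but no bands, channels or regions are listed. The Discussion's three connections ("Specifically, we predict enhanced connectivity between") are not assigned to fMRI in that passage; counting them there is an assumption.
- Pairwise contrasts on continuous measures are not left uncorrected. Item (4) carries over the primary outcome's corrected post-hoc comparisons, so any error figure built on uncorrected contrasts would be too high.
- The exact family and list of metrics are details that an article commonly leaves to the analysis plan, which is not shown.

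A reader might also take the Discussion's mechanism sentence as a confirmatory claim at 5%. It speaks of triangulating several measures and promises no family-wise control.

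**Conclusion.** The point holds as a better method, not as an error. At the same 5% family-wise level and under any correlation, Holm rejects at least as much as the stated rule. Under the assumptions above, the gain in average power is about 10 to 12 percentage points if all five effects are real at a difference of 0.8, about 4 to 5 points if three are, and essentially nil if one is. It is about 3 to 4 points if all five are real at 0.548. The ranking of the two methods rests on no assumption; the size rests on the number of tests, the assumed effects and the two-arm simplification. A failure to control 5% is not shown. The conditional range of 0.04 to 0.10 is only a reason to be clear about which tests the rule covers.

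**What to change.** In the last paragraph of Statistical methods, replace the Bonferroni correction with Holm's procedure at two-sided 5% for the secondary p-values, applied to the between-group test of each secondary endpoint within the existing three-group analysis. Make the same substitution in the subgroup rule of item (6). In item (4), label the within-group tests and any additional metrics exploratory, as item (6) already does for subgroups. The three-group comparison itself stays as it is.

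The cost is a few words, agreed before unblinding; no patients, visits or data are added. The downsides are the simultaneous intervals noted above, so intervals would be reported unadjusted and described as such, and fewer metrics would sit inside the controlled family.
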